**Discussion:**

Subcutaneous tunneling is a widely used method to reduce complications associated with catheters. However, its application in PICC has not yet been extensively explored, especially in Brazil. A randomized clinical trial is necessary to objectively assess the effects of subcutaneous tunneling in PICC insertion. This protocol aims to provide evidence on the effectiveness of this technique in reducing complications.

**Trial registration:**

Clinical Trials platform NCT06365528

## Introduction

The use of peripherally inserted central catheters (PICCs) has grown in recent years due to their advantages over other catheters. Research highlights benefits such as longer dwell times, durability, safety, comfort, versatility [1,2], and cost-effectiveness [3]. Industry advancements in materials (polyurethane, polyethylene) and technology have further driven adoption. Innovations include tip navigation and location systems [4], ultrasound, micro-introduction, and the Modified Seldinger Technique [5,6].

However, despite all these technical advancements and the deepening of knowledge related to the use of PICC, this device is not free from risks. Major complications, such as thrombosis and infection, and minor complications, such as phlebitis, accidental traction, and catheter displacement, can occur at varying rates depending on the study population. In adults, studies indicate catheter-related infection rates ranging from 0.07 to 2.46 per 1000 catheter-days, which are more common in oncology and intensive care patients [7,8].

Regarding thrombosis, patients with hematologic cancer are more predisposed to this condition, with incidence rates varying from 2% to 75% [9–12]. However, it is noteworthy that these rates can be reduced with the use of higher-quality devices, advanced technology, vascular access specialist nurses, and the adoption of best practices in both insertion and maintenance [13]. A multicenter study conducted in 16 centers in Brazil on patients with PICCs supports these findings, showing low complication rates, such as catheter-related bloodstream infection, venous thrombosis, and reversible occlusion [14].

While technology, vascular access teams, best practices, and infection control bundles have reduced PICC-related complications, new insertion techniques can further minimize risks. Studies support the tunneling technique over conventional insertion [15,16]. A randomized clinical trial (RCT) found tunneled PICCs had longer dwell times and lower thrombosis and infection rates [16], with another RCT confirming reduced thrombosis and accidental tractions [17].

Based on this, we understand that there is a lack of studies with robust methodologies, especially those with larger sample sizes, to corroborate the current results. Similarly, few studies demonstrate the combined impact of tunneled PICC insertion on reducing negative outcomes. Therefore, we test the hypothesis that tunneled PICCs have lower rates of the combined or isolated outcomes like catheter-related bloodstream infections, thrombosis, occlusion, and accidental traction compared to PICC inserted using the conventional technique in the adult population of three large hospitals involved in the RCT.

## Methods

### Study design

This is a randomized, parallel, multicenter clinical trial, blinded to the allocation groups during the analysis of the primary outcome, conducted in three hospitals in Brazil. This study has been registered on the Clinical Trials platform under NCT06365528.

### Participants and eligibility criteria

The study will include adult patients (≥ 18 years) admitted to medical-surgical and intensive care units with an indication for PICC, regardless of the number of lumens or catheter gauge. Patients will be excluded from the study if they do not have suitable venous conditions for safe PICC insertion, which means occupancy rate >45% in the green zone (according to the Zone Insertion Method) [18]; patients with chronic kidney disease, whether on dialysis or not; patients in a critical or unstable condition; or patients with cognitive deficits that impair their understanding of the study and who do not have a responsible person to assist at this stage.

### Settings and location

This multicenter RCT will be conducted in three hospitals in Porto Alegre, RS, Brazil (Hospital de Clínicas de Porto Alegre, Santa Casa de Misericórdia de Porto Alegre and Hospital Moinhos de Vento), from May 2024 to December 2025. All centers are large, tertiary hospitals that offer the best care for various health conditions. Additionally, they have dedicated teams of nurses specializing in vascular access and infusion therapy.

### Groups and Interventions Intervention description

The patients recruited for the study will be randomly divided into two groups: Intervention Group (IG) – adult patients who will have the tunneled PICC insertion; and Control Group (CG) – adult patients who will have the PICC insertion performed using the conventional technique (non-tunneled).

When an adult patient requires a peripherally inserted central catheter (PICC), the medical or nursing team will notify researchers via an electronic system or medical prescription, providing patient details. The research team will assess eligibility, invite qualifying patients, and obtain informed consent. Participants will be randomly assigned to: a) PICC insertion using the tunneling technique (Intervention Group), or b) PICC insertion using the conventional technique (Control Group). Non-participants’ data will be stored in a database of potentially eligible patients. Research team nurses with tunneling expertise will perform the Intervention Group procedures, while hospital nurses unaffiliated with the research team will handle the Control Group procedures.

The catheters inserted in the Control Group will follow the routine procedure of each institution, according to their respective Standard Operating Procedures (SOP), with ultrasound-guided puncture and modified Seldinger technique. The procedures for the Intervention Group, in addition to the conventional PICC insertion technique, will include the additional steps of catheter tunneling, as described below (S2 Fig):

### Outcomes

**Catheter-related primary bloodstream infection:** bloodstream infection in a patient using a peripherally inserted central catheter (PICC) for more than two days (with the first day being the day of catheter insertion) and diagnosed with infection either while the catheter is still in use or within one day after its removal [19].

**Catheter-related thrombosis:** formation of thrombi inside the vein leading to obstruction of blood flow. Diagnosis should be made using appropriate imaging exams (venous ultrasound and/or venous Doppler), associated or not with the following signs and symptoms: pain, swelling, redness, dilated superficial veins, impaired limb movement, low-grade fever [20].

**Irreversible catheter occlusion:** Catheter occlusion is characterized by the blockage of the lumen due to the formation of a blood clot or precipitate of medications, preventing the infusion of intravenous solution [20].

**Accidental catheter dislodgement: C**haracterized by the accidental partial or total exteriorization of the catheter by a healthcare team member or the patient themselves, rendering the catheter unusable. Inviability of the catheter is defined by the improper positioning of the distal end of the catheter outside the cavoatrial junction, where positioning of the catheter is mandatory [20].

### Participant timeline

See S3 Table.

### Sample size

The sample size calculation considered a composite outcome including primary bloodstream infection related to the catheter, thrombosis, catheter obstruction, and accidental catheter traction. Sample size was calculated to detect differences in proportions between the control and intervention groups using the online tool PSS Health version [21], with a statistical power of 80%, a significance level of 5%, and a relative risk of 0.5 [22], indicating a 50% reduction in composite outcomes. The calculated sample size, with an additional 10% for potential losses, totals 840 subjects, divided equally (420 each) between the two groups across the three institutions.

### Recruitment

When an adult patient needs a peripherally inserted central catheter (PICC), the medical or nursing team will notify researchers via electronic systems or medical prescriptions with patient details. The research team will assess eligibility, invite qualifying patients, and obtain informed consent. Participants will be randomly assigned to study groups. Recruitment started on May 6, 2024 and will be completed on December 31, 2025. The data collection will be finished in 30 days after the last inclusion.

### Randomization Sequence generation

Participants, after giving informed consent, will be randomly assigned to either the Intervention Group or the Control Group. Randomization will be generated using a dedicated tool within the REDCap software, in blocks of varying sizes. Each participating center will manage the randomization of their participants. The strategy of varying block sizes will be employed to ensure allocation concealment.

### Implementation

The allocation sequence of participants in the study will be digitally and automatically conducted using the REDCap software. One researcher from each participating center, blinded to the data collection phase of the research, will be responsible for generating the sequence. Participant enrollment in the study will be carried out by the researchers responsible for implementing the study at each participating center.

### Blinding

After group assignment, the researchers at each participating center responsible for data collection, whether in person or virtually (via electronic medical records), will be blinded to the allocation of each participant. Study patients will be instructed by the research team that conducted the allocation not to disclose which intervention was received.

The researchers responsible for outcome analysis, as well as the statistical team involved in the analysis, will be blinded since they will not be involved in the recruitment, allocation, or data collection stages.

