## Discussion

Subcutaneous tunneling is a well-established technique that has been widely employed in various medical procedures to reduce the risk of complications associated with the placement of catheters. This method involves creating a tunnel beneath the skin through which the catheter is passed before entering the vein, thereby increasing the distance between the catheter’s entry point into the vein and its exit site on the skin. This added distance can serve as a protective barrier against microbial contamination, potentially reducing the incidence of catheter-related infections and improving overall catheter stability.

Despite its proven benefits in other types of vascular access, the application of subcutaneous tunneling in PICCs remains underexplored, particularly within the Brazilian healthcare context. PICCs are commonly used for medium- to long-term intravenous therapy, especially in patients requiring extended antibiotic treatment, parenteral nutrition, or chemotherapy. Given their widespread use and the associated risk of complications such as infections, thrombosis, and catheter dislodgement, exploring new strategies to enhance their safety and effectiveness is of great clinical importance.

Currently, there is a lack of robust, high-quality evidence evaluating the impact of subcutaneous tunneling specifically in PICC placements. While unsystematic reports and smaller studies suggest potential benefits, the absence of large-scale randomized clinical trials limits the ability to draw definitive conclusions about the technique’s effectiveness in this setting. This is especially true in Brazil, where there are significant regional differences in healthcare infrastructure, infection control practices, and patient populations.

To address this gap in the literature, a randomized clinical trial is necessary to objectively assess the outcomes of PICC insertion with and without the use of subcutaneous tunneling. Such a study would provide valuable data on whether this technique can indeed reduce complications such as infection, thrombosis, or catheter malfunction in Brazilian patients.

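### Data collectors are said to be blinded, but the design as described does not support this for in-person collection, where tunneling changes the visible exit site and the only safeguard is patient silence

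*Protocol article*

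**What the plan says.** The Blinding section makes two claims.

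- **Data collectors.** After assignment, the researchers "responsible for data collection, whether in person or virtually (via electronic medical records), will be blinded to the allocation of each participant". The measure offered in support is "Study patients will be instructed by the research team that conducted the allocation not to disclose which intervention was received".
- **Outcome researchers and statisticians.** They "will be blinded since they will not be involved in the recruitment, allocation, or data collection stages".

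The Study design section is narrower. It calls the trial "blinded to the allocation groups during the analysis of the primary outcome" and does not mention data collection.

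Three other sections bear on whether the collector claim can hold.

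- **Discussion:** tunneling increases the distance between the catheter's "entry point into the vein and its exit site on the skin".
- **Groups and Interventions:** "Research team nurses with tunneling expertise will perform the Intervention Group procedures, while hospital nurses unaffiliated with the research team" carry out the control insertions.
- **Outcomes:** accidental dislodgement covers partial as well as total exteriorization. For thrombosis, "Diagnosis should be made using appropriate imaging exams (venous ultrasound and/or venous Doppler), associated or not with the following signs and symptoms" that the section goes on to list.

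**The concern.** Blinding of observers is a property that readers and meta-analysts rely on when they judge bias. Here it is asserted for people who may examine the arm of a patient whose catheter leaves the skin at a different place depending on allocation. A request that patients stay silent blocks one route to unblinding. It does nothing about what can be seen at the exit site, or about who performed the insertion if the collector learns it.

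The primary outcome is a composite whose components reach the data set through human steps: someone asks for an ultrasound, draws a culture, or notes that a catheter has moved. If those steps, or the later classification, differ with knowledge of the arm, the comparison is biased. The trial report would also claim a protection that it did not have.

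**Working it through.** **Step 1. Compare the claim with the rest of the article.**

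| Route to the arm | What the article says | Does patient silence close it? |
|---|---|---|
| Patient tells the collector | Blinding: patients are asked not to | Yes, if they comply |
| Collector sees the exit site | Discussion: tunneling displaces it from the vein entry point; no concealing dressing is described | No |
| Collector learns who inserted | Groups and Interventions: inserters differ by arm | No |
| Collector reads the insertion note | Not stated; inferred, because collectors use the electronic record and insertion is a procedure one expects to be charted | No |

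The second row decides the matter for in-person collection, because partial exteriorization is assessed at the place that shows the technique. The third row matters only if the collector learns the inserter's identity. The fourth is inference.

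**Step 2. Ask what the blinded outcome researchers can protect.** They can protect classification, provided the material they read does not show the arm. They cannot recover a thrombosis that was never imaged or an event that was never recorded.

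**Step 3. Illustrate the possible size.** The article gives no blinding-related figure to reproduce. It also gives no control event rate, so the sample size of 840 cannot be reproduced directly. Solving backwards with its stated inputs (80% power, two-sided 5%, relative risk 0.5, 10% for losses, 1:1):

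- A control risk of 11.3% against 5.65% needs 381 per arm by the pooled-variance formula without continuity correction. 381 × 1.1 = 419.1, rounded up to 420 per arm, or 840.
- Totals within 3% of 840 arise for control risks of about 11.0-11.7% without continuity correction, or 12.0-12.6% with it.

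The 11.3% is therefore an assumption that fits, not a figure from the plan.

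Let p be the true risk in both arms (no effect), and let a fraction f of tunneled-arm events go unrecorded. Then p2 = p(1 − f), d = p − p2, and p̄ = (p + p2)/2. With n per arm,

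- SE0 = √[2p̄(1 − p̄)/n]
- SE1 = √[p(1 − p)/n + p2(1 − p2)/n]
- P(reject) = Φ[(d − 1.96·SE0)/SE1] + Φ[(−d − 1.96·SE0)/SE1]

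Example: p = 0.113, f = 0.20, n = 378 (420 less 10%). Then p2 = 0.0904, d = 0.0226, p̄ = 0.1017, SE0 = 0.02199 and SE1 = 0.02197. The first term is Φ(−0.933) = 0.1755 and the second is about 0.0014, giving 0.177.

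| Assumed control risk | n per arm | f = 10% | f = 20% | f = 30% |
|---|---|---|---|---|
| 10% | 378 | 0.076 | 0.160 | 0.315 |
| 10% | 420 | 0.078 | 0.173 | 0.344 |
| 11.3% | 378 | 0.079 | 0.177 | 0.353 |
| 11.3% | 420 | 0.083 | 0.191 | 0.385 |

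Here f applies to the whole composite. If only some components are open to influence, f is their share of events times the under-recording within them. For instance, if they made up half the events (assumed), 20% under-recording within them would give f = 0.5 × 0.20 = 10%.

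**Step 4. Workload of redacted classification.** At 11.3% and 5.65%, expected events are 378 × (0.113 + 0.0565) ≈ 64, or 420 × 0.1695 ≈ 71. With no effect they are 2 × 378 × 0.113 ≈ 85, or 2 × 420 × 0.113 ≈ 95. These count true events. Suspected events would be somewhat more numerous.

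**The case against.** The best counter-argument is that this is a condensed article. The tunneling steps, S2 Fig and S3 Table are not in the text at hand, and details of dressings, chart access or database masking normally sit in the full protocol. A dressing might hide the exit site, and a collector might never learn who inserted the catheter. This stands as a limit on certainty: the documents do not prove that collectors are unblinded. It does not rescue the claim. The article affirmatively states blinding for in-person collection, names one safeguard, and that safeguard does not address the visible difference that the article itself describes.

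Several stronger readings are tempting, but the text does not support them.

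- **The chart discloses the arm.** This is plausible, but no section says so.
- **Dislodgement is a matter of staff opinion.** The Outcomes section requires the catheter to be unusable and ties this to the tip lying outside the cavoatrial junction, which is an anatomical criterion. Noticing the event may depend on the observer; the definition is not free judgement.
- **The plan claims that patients, inserters or ward staff are blinded.** It does not. Asking patients not to disclose presupposes that they know.
- **The analysts are unblinded.** The article says that they are blinded and separate from earlier stages. Separation alone does not hide the arm in what they read, but coding and redaction details are commonly left to fuller documents. They belong in the remedy, not in the charge.
- **The primary outcome should count only thrombosis imaged for symptoms.** This would tie the endpoint to symptoms reported by patients who know their arm, and would change the primary outcome after recruitment began in May 2024.

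**Conclusion.** The concern holds in a limited form. The statement that in-person data collectors are blinded is not supported by the design as described, and for collectors working from the electronic record it is doubtful by inference. It should be corrected, because the trial report would otherwise inherit it.

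The size of any resulting bias is unknown. The rates of roughly 8%, 16-19% and 32-39% rest on an assumed control risk of 10-11.3%, 378-420 patients per arm, no true effect, and assumed under-recording of 10%, 20% and 30% across the whole composite in one arm only. The assumed direction, in favour of tunneling, is plausible because research-team nurses perform only that procedure, but the documents do not establish it. The figures show that modest differential recording would matter in a trial of this size. They do not show that it will occur.

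**What to change.** 1. **Correct the claim.** Withdraw the statement that data collectors are blinded, or restrict it to collectors who neither see the insertion site nor read the insertion record.
2. **Protect classification.** Have the outcome researchers already named in the Blinding section classify every suspected event against the Outcomes definitions, using extracts from which technique, inserter and exit-site description have been removed. Catheter tip position can stay in, since the dislodgement definition needs it. Someone other than the classifiers must prepare the extracts.
3. **Code the arms** in the data given to the statisticians.
4. **State the remaining limitation.** These steps protect classification, not detection. Whether imaging or cultures are requested can still depend on staff who know the arm, unless S3 Table schedules the same assessments in both arms. If it does, say so.
5. **Leave the thrombosis definition unchanged.**

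The cost is a wording amendment, a less favourable blinding statement, and redaction for a number of suspected events somewhat above the 64-95 true events expected under the assumptions used here. It uses people already in the plan and can be applied to records already collected, so ongoing recruitment is no obstacle.

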### Statistical methods

The data will be entered and analyzed using the Statistical Package for the Social Sciences (SPSS) version 24.0. Initially, a Shapiro-Wilk test will be conducted to assess the normality of continuous variable distributions. Following this stage, a descriptive analysis will be performed, in which results will be reported as mean ± standard deviation (SD), median (P25 - P75), or as absolute and relative frequencies, depending on the characteristics and distribution of the variables.

The quantitative variables between groups will be compared using either Student’s t-test or the Mann-Whitney U test, depending on the data distribution. Pearson’s Chi- square test will be employed to assess associations between the clinical characteristics of patients and devices with events during follow-up. Groups will be compared for device event-free survival using Cox proportional hazards analysis and the log-rank test.

Other associations will be analyzed based on data distribution and appropriate statistical tests. A two-tailed P < 0.05 will be considered statistically significant.

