**Materials and methods:**

In this randomized, parallel, multicenter clinical trial, 840 patients from three reference hospitals will be assigned to two parallel groups (conventional PICC and tunneled PICC groups) through computer-generated stratified randomization. The conventional group will undergo PICC insertion according to routine practice. In the tunneled PICC group, an additional subcutaneous tunneling procedure will be performed. Patients will be followed until PICC removal for any reason or 30 days after insertion, whichever occurs first. The primary outcome is to assess whether subcutaneous tunneling reduces the rate of isolated or combined adverse events (infection, thrombosis, obstruction, and dislodgement) compared to the conventional method.

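### Randomisation is stratified and run within centre, but the named log-rank and Cox comparison carries no centre stratification: a small, conservative loss that one sentence removes

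*Protocol article*

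**What the plan says.** The abstract (Materials and methods) states that patients are assigned "through computer-generated stratified randomization" but does not name the stratification factor. The section on sequence generation adds: "Randomization will be generated using a dedicated tool within the REDCap software, in blocks of varying sizes" and "Each participating center will manage the randomization of their participants". The Implementation section has one researcher per centre produce the sequence. Together these make centre a stratum in practice.

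Statistical methods gives the group comparison as "Groups will be compared for device event-free survival using Cox proportional hazards analysis and the log-rank test". Neither centre nor any stratification factor or covariate is attached to it. Significance is set by "A two-tailed P < 0.05 will be considered statistically significant".

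The Sample size section compares two proportions, "with a statistical power of 80%, a significance level of 5%, and a relative risk of 0.5". It adds 10% for losses and arrives at 840 patients, 420 per arm, with no mention of strata.

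**The concern.** Blocking within centre forces the arms to be nearly equal in each hospital, so differences in risk between hospitals cannot contribute much chance imbalance to the treatment comparison. An analysis without centre still computes its variance as if they could. Where hospitals differ in risk, the reported standard error then exceeds the true spread of the estimate, and the test rejects less often than its nominal level. Leaving out a prognostic centre effect also pulls the estimated hazard ratio slightly towards 1.

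Some difference between hospitals is possible, because control insertions follow each institution's own operating procedures. At stake is a little power in a trial sized at 80% for a halving of risk. The validity of a positive result is not at stake.

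**Working it through.** **Planned sample size.** The control event risk is not given, so 840 cannot be rebuilt from the stated inputs alone. It can be back-solved from the usual two-proportion formula with pooled variance under the null:

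n per arm = [1.960·√(2p̄(1−p̄)) + 0.842·√(p₁(1−p₁) + p₂(1−p₂))]² / (p₁−p₂)²

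With p₁ = 0.1137, p₂ = 0.05685 and p̄ = 0.0853, this is (0.774 + 0.331)² / 0.00323, or about 378. Then 378/0.9 = 420 per arm, which gives 840. A control risk near 11.4% is therefore consistent with the plan. With a continuity correction it would be about 12.3%. The sample size is not shown to be wrong, and the point does not depend on it.

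**Simulation inputs.**
- From the document: three centres, 1:1 allocation, varying blocks, two-sided 5%, 30-day follow-up, and 840 less 10% = 756 evaluable patients.
- Assumed: 756/3 = 252 per centre, block sizes 2/4/6, exponential event times, hazard ratio 0.5, no censoring before day 30, and the control risks shown below (each set averages 11.3% to 11.4%).

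**Method.** The daily control hazard in centre k is −ln(1−p_k)/30. The test statistic is Z = Σ(O_k−E_k)/√ΣV_k, summed over centres for the stratified test and computed as one stratum for the unstratified test. The one-step log hazard ratio is Σ(O−E)/ΣV, with reported SE (ΣV)^(−1/2). There were 10,000 runs per scenario. Simulation error is √(0.05·0.95/10,000), about 0.2 points, for type I error, and √(0.78·0.22/10,000), about 0.4 points, for power.

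| Assumed control risks | Type I error, unstratified vs stratified | Power, unstratified vs stratified |
|---|---|---|
| 11.4% in all centres | 5.0% vs 5.1% | 78.3% vs 78.3% |
| 8/11.4/14.8% | 4.7% vs 4.8% | 78.2% vs 78.4% |
| 4/10/20% | 4.9% vs 5.3% | 77.5% vs 78.4% |
| 2/7/25% | 4.1% vs 5.2% | 76.3% vs 78.7% |

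Power is a little under 80% even with identical centres. One reason is that a hazard ratio of 0.5 at 11.4% is a risk of 1 − 0.886^0.5 = 5.87%, a relative risk of 0.0587/0.114 = 0.515 and not 0.5.

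**Standard errors under the null (unstratified).** Mean reported SE against actual SD of the log hazard ratio:
- 8/11.4/14.8%: 0.216 vs 0.215
- 4/10/20%: 0.217 vs 0.214 (ratio 1.014)
- 2/7/25%: 0.217 vs 0.208 (ratio 1.043)

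With stratification the last pair is 0.217 vs 0.219.

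**Cross-check on 30-day risks.** Pooled chi-square against centre-stratified Mantel-Haenszel, 60,000 runs, 126 per arm per centre:
- 5/11/18%: type I error 4.6% vs 5.0%, power 80.9% vs 81.5%
- 3/8/23%: type I error 4.2% vs 5.1%, power 81.3% vs 82.8%

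The direction and order of size are the same.

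**The case against.** The strongest objection is that the article is silent and has not made a choice. It does not say the tests are unstratified, a Cox model can carry strata, and model terms often stand in an analysis plan that is not shown. That stands in part: a reader might infer that the plan ignores centre or rules out adjustment, and the text supports neither. What remains is that the article names both the design feature and the test, and does not connect them.

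Second, the three sites are large tertiary hospitals in one city, each with a specialist vascular-access nursing team. No differing case mix is stated and no centre rates are given. This also stands. The wider spreads are illustrations, and a 2% to 25% range is extreme.

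Third, stratifying does not shrink the reported Cox standard error. In a separate simulation of 6,000 runs, the mean SE at hazard ratio 0.5 was 0.2650 unstratified and 0.2651 stratified (5/11/18%), while power moved from 76.1% to 76.7%. This is correct. The gain comes mainly from a less attenuated hazard ratio, so a claim of narrower Cox intervals would be wrong.

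Two further inferences are tempting and do not hold:
- **Risk groups.** The Introduction says of infections "which are more common in oncology and intensive care patients" and of thrombosis "patients with hematologic cancer are more predisposed to this condition". A reader might take the omission of these groups as a mismatch with the design. They are background only and are never named as strata, and a comparison without them is valid. Adjustment could help. With an assumed factor of 30% prevalence and hazard ratio 3, added to 4/10/20% centres, power was 75.0% unstratified, 75.9% stratified by centre, and 77.6% stratified by centre and factor. That is an optional gain.
- **Covariate screening.** A reader might see the planned chi-square tests of characteristics against events as a screen for Cox covariates. The article describes them as tests of association and does not link them to the model.

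**Conclusion.** The point holds as a minor, free improvement: the analysis should follow the groups within which the trial randomises. Under assumed centre risks, leaving centre out costs from nothing to about 1.1 points of type I error (4.1% vs 5.2%) and up to 2.4 points of power (76.3% vs 78.7%). The top of that range needs a more than twelvefold spread between hospitals (25/2 = 12.5). At modest spreads the difference is within simulation error. Any distortion is conservative, so it would not create a false claim of benefit.

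The result rests on equal centre sizes, exponential times, small blocks, no early censoring and an average control risk near 11.4%. The article gives none of these. It also rests on reading centre as a stratum, which the within-centre randomisation supports although the stratification factor is not named.

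**What to change.** In Statistical methods, add: *The primary log-rank test and Cox model will be stratified by centre and by any other factor used to stratify the randomisation.* In the randomisation section, name the stratification factor or factors.

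If 30-day risks are also compared, use Mantel-Haenszel by centre. Adjustment for cancer or intensive care status is optional. If it is wanted, fix the covariates before unblinding.

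The cost is one sentence. Centre is known for every participant, SPSS offers both stratified analyses, and N stays at 840. Sparse strata are unlikely with centre alone: at an 11.4% control risk and relative risk 0.5, about 378 × 0.114 × 1.5 = 65 events are expected, or roughly 22 per centre if spread evenly.
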